### Sample size and statistical power

We plan for a total sample size of 112 children (80% power to detect a mean effect difference of 15 between groups on the quality of life scale) at 0.05 significance level. This sample size has been adjusted for an anticipated high attrition rate of 50%. A 2-sample test of proportions will be used to compare baseline characteristics of both groups.

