**Methods:**

An open, unblinded, multi-centre randomised controlled trial in two Australian public hospitals. 112 children (0–16 years) fulfilling the inclusion criteria will be randomised to one of two clinical pathways for management of their chronic health condition: (1) integrated children’s care clinic (ICCC) or (2) self-directed care pathway. All children and caregivers will be interviewed at 1 week, and 3, 6 and 12 month time intervals. Primary outcome measures include the Pediatric Quality of Life (PedQOL) questionnaire, Subjective Units of Distress Scale, Child Behaviour Checklist (CBCL) and Rotter’s Locus of Control Scale. Secondary outcome measures include the total number of medical appointments, school days missed and quantity of services accessed. Our main objectives are to determine if the ICCC results in better health and economics outcomes compared to the self-directed care pathway.

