### Randomisation

A randomisation list, created by an independent biostatistician will be used. Block size permutation of *n* = 7 will be utilized to ensure equal distribution of participants into each pathway. Assessment allocation (ICCC versus self-directed care pathway) will be concealed in sequentially numbered opaque envelopes and assigned to enrolled children immediately after informed consent is gained to participate in the research trial by the AHLO. The envelope will be opened in front of the caregiver and child. This would mean that the caregiver, child and AHLO involved in the trial will not be blinded to group assignment. Blinding in this trial is not feasible due to the nature of the ICCC pathway (i.e. caregivers will expect a multidisciplinary appointment with a General Practitioner).

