#### Outcome measures

Primary outcome measures taken at 1 week, 3, 6, 12 months include**:** PedQOL child module (Score 0 to 100; parent or child completed), [20] PedQOL family impact module (Score 0 to 100; parent completed), [20] SUDS (Score 0 to 100; parent completed), CBCL (Percentiles, parent completed) [21] and Rotter’s Locus of Control Scale (Score 0 to 23, parent completed) [22].

Secondary outcome measures taken at 1 week, 3, 6, 12 months include the number of**:** GP visits, hospital admissions**,** specialist appointments**,** absent school days, caregiver missed employment days, school suspensions including duration in days and services currently accessed at the time.

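### Five co-equal primary outcomes share one 0.05 level and a sample size set for one unnamed quality-of-life scale, so 5% overall error and 80% power cannot both hold for the primary set

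*Protocol article*

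**What the plan says.** Under Outcome measures, the list opens "Primary outcome measures taken at 1 week, 3, 6, 12 months include" and then gives five scales: the PedQOL child module, the PedQOL family impact module, SUDS, CBCL and Rotter's Locus of Control. None is marked as leading, and no visit is singled out. The abstract does the same: it puts "Subjective Units of Distress Scale, Child Behaviour Checklist (CBCL) and Rotter’s Locus of Control Scale" beside the PedQOL as primary. The rater of the child module is left open: "PedQOL child module (Score 0 to 100; parent or child completed".

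Under Sample size and statistical power there is one justification. "We plan for a total sample size of 112 children", for "80% power to detect a mean effect difference of 15 between groups on the quality of life scale", "at 0.05 significance level", inflated for 50% attrition. No module, visit, SD or sidedness is given.

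Under Statistical analyses, a Mann-Whitney U test is named for quality-of-life measures, in the plural. No test is named for SUDS, CBCL or Locus of Control. Hypothesis (a) under Aims nevertheless claims better behavioural scores as well as better quality of life.

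The visit-by-visit procedures for the ICCC pathway, which the self-directed pathway largely follows, give a thinner schedule than the outcome list. The two PedQOL modules, SUDS and Locus of Control are collected at 1 week, 6 and 12 months, and CBCL at 3 and 6 months only.

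**The concern.** The label primary attaches to five scales at several visits, but the size calculation covers one comparison. A reader cannot tell which comparison the 80% describes, because two PedQOL modules and three PedQOL visits all fit the sentence. Nor can a reader tell what the 0.05 protects.

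This matters more here than in a blinded trial. Allocation is known to caregiver, child and AHLO, the outcomes are mostly parent-reported, and half the children are expected to be lost. If no endpoint is fixed beforehand, whichever scale, rater or visit turns out favourable can be presented as the primary result. A null result can likewise be offset by any one of the other primaries.

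**Working it through.** **Inputs.** Total 112, difference 15, power 80%, alpha 0.05 and attrition 50% (Sample size and statistical power). Equal allocation (Randomisation: "to ensure equal distribution of participants into each pathway"). Two-sided testing is assumed. The SD is not stated.

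**The plan's own figure.**
- Evaluable: 112 × (1 − 0.5) = 56, or 28 per arm.
- n per arm = 2 × (1.96 + 0.84)² × (SD/15)². With SD 20 this is 27.9, rounded up to 28. Then 2 × 28 / 0.5 = 112.
- SD 20 therefore matches exactly, but it is back-solved and does not independently reproduce the figure. Other routes also give about 112: a one-sided test with SD about 22.6, or a Mann-Whitney inflation with SD 19.
- Power for one unadjusted comparison at SD 20 and 28 per arm: 80.1% (normal), 78.7% (t-test), about 76% (Mann-Whitney, simulated). At SD 19 the simulated Mann-Whitney power is 80%.

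**Number of comparisons.**
- Outcome measures list: 5 scales × 4 visits = 20.
- Procedures: 4 scales × 3 visits + CBCL × 2 visits = 14.

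**Chance of at least one false positive, each test at two-sided 0.05.** For independent tests this is 1 − 0.95^k. Correlated values come from simulating equally correlated normal statistics.

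| Tests | Independent | Correlation 0.5 | Correlation 0.7 |
|---|---|---|---|
| 2 PedQOL modules, one visit | 9.8% | 9.1% | 8.3% |
| 5 outcomes, one visit | 22.6% | 18.4% | 14.8% |
| 14 scheduled comparisons | 51.2% | 34.7% | 24.7% |

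These rates count false findings in either direction. For false benefit alone, five independent tests give 1 − 0.975^5 = 11.9%, and about 7% at correlation 0.7.

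**Power if the 5% is protected by splitting alpha** (SD 20, 28 per arm).
- Standardised signal: (15/20) × √(28/2) = 2.806.
- Five outcomes, alpha 0.05/5 = 0.01, critical value 2.576: power = Φ(2.806 − 2.576) = Φ(0.230) = 59%. The t-test gives 56% and the simulated Mann-Whitney about 52%.
- Two modules, alpha 0.025: 71% (normal).
- Sensitivity for five outcomes (normal): 71% at SD 18, 37% at SD 25.
- Restoring 80% with five outcomes at alpha 0.01 takes 42 per arm evaluable, so 2 × 42 / 0.5 = 168 children in place of 112.

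An equal split is conservative when outcomes are correlated, so these powers are the pessimistic end.

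**The case against.** The best counter-argument is that the protocol nowhere says all five outcomes are tested at 0.05 at each visit. The 0.05 appears only in the sample-size sentence, a test is named only for quality of life, and a multiplicity rule may sit in an analysis plan that is not shown. This stands in part. Testing all five at 0.05 is inferred from the primary label and the only alpha given, and the absence of an adjustment method is not the finding. But the choice of primary endpoint is made in this document, and it chooses five. Even the narrowest reading, two PedQOL modules at one visit, exceeds 5%.

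Four stronger readings are tempting, and the document does not support them.

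- *Neither the 5% nor the 80% holds.* For one unadjusted quality-of-life comparison the 80% holds to within a few points at SD 20. Unadjusted testing loses only the overall 5%; splitting alpha loses only power.
- *Twenty tests, with an error rate of 64%.* This takes the outcome list at face value and ignores the procedures, which schedule 14.
- *A false claim of benefit is several times more likely than 5%.* The familywise rates are two-sided. For five outcomes at one visit, false benefit is 7-12%.
- *The trial is underpowered because Mann-Whitney is used.* That rests on a back-solved SD. At SD 19 the test reaches 80%.

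It could also be said that the open rater is dealt with: the procedures have the caregiver complete the PedQOL by telephone, and the Discussion foresees a mix of parent and child report according to age, development and cognition. That explains the intention, but does not say whose score is the primary one.

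**Conclusion.** The concern holds in this form: the declared primary set has no lead outcome, rater or visit, and its sample size was justified for a single unnamed quality-of-life comparison. For that set, 5% overall error and 80% power are incompatible. The cost is either an overall two-sided error of about 8-10% (two modules, one visit), 15-23% (five outcomes, one visit) or 25-51% (14 comparisons), or power of about 52-59% when alpha is split over five outcomes. No power is shown for SUDS, CBCL or Locus of Control.

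The error rates assume each test is run at two-sided 0.05, with correlations between 0 and 0.7. The power figures assume SD 20, 28 evaluable children per arm and roughly normal scores. The main conclusion, that one endpoint must be named, depends on none of these assumptions. It should be settled before any comparative analysis.

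**What to change.** 1. Name one PedQOL module, one rater and one visit as the single primary endpoint, tested at two-sided 0.05. The child module, parent-reported, at 6 months fits the plan. It is already scheduled then, one rater serves all ages, and it comes before the pathway change that is allowed after 6 months and removes switchers' 12-month data (Safety considerations/patient safety).
2. Move the other four scales, child self-report and the other visits to secondary.
3. Reconcile the visits under Outcome measures with those in the pathway procedures.
4. State the SD, the test and the visit behind 112, so that the 80% refers to that endpoint.

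Baseline adjustment should not be counted on to recover power. Envelopes are opened immediately after consent, and the PedQOL is first scheduled at the 1-week contact, so no pre-randomisation score is described.

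The cost is that four outcomes lose the label primary, and that an ethics and registry amendment is needed in a trial that began recruiting in October 2017. No extra children are needed. Keeping five co-equal primaries with an equal split of alpha would take about 168 at SD 20.

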### Statistical analyses

All analyses will be conducted using an “intention to treat” (ITT) analysis where all subjects will be compared in the groups which they were originally assigned (regardless of withdrawal or lost to follow-up). For our primary objective, Mann Whitney U test will be used to determine if differences in quality of life measures exist between the ICCC versus self-directed care groups.

For our secondary objective, we will perform univariable analysis to determine which health economic parameters (e.g. missed school days, number of hospital admissions) are related to higher quality of life scores. Stepwise regression will then examine the various combinations via of health economic parameters to generate area under receiver operating curves (aROC) to determine a clinical prediction index for higher quality of life scores. Parameters chosen will be based on using factors that were significant plus those with *P* < .25 level in the univariable analysis and other variables known to have a strong association with poorer health outcomes (e.g. multiple co-morbidities) within the literature. An aROC of ≥0.75 will be considered a clinically relevant cut-off score [23].

As this study is registered on the ANZCTR and occurring within Metro North Hospital and Health Service, the trial may be randomly audited by an independent study monitor at any timepoint in the study. A data monitoring committee will not be set up for the purposes of this study, as it is unblinded and not comparing rates of mortality or major morbidity.

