### Recruitment

Children attending paediatric outpatient clinics with the Paediatrician at Caboolture Hospital or GCUH will be approached to participate in the study at the conclusion of their medical appointment by the Allied Health Liaison Officer (AHLO). The caregivers will be provided with a parent information sheet (Additional file 1) and study brochure and informed consent will be gained at this time with or as close as possible to this time. The researcher will verbally explain the caregiver information sheet, study brochure and consent form for all caregivers of eligible participants. If parents/caregivers consent for their family to be part of the study, then they will be asked to sign the consent form and initial and date each page of the caregiver information sheet and study brochure to acknowledge that they have understood the study requirements. When necessary, particularly for children of non-English speaking backgrounds, interpreter services will be used to aid in providing informed consent.

For caregivers who identify with literacy issues, the AHLO will ensure extra time is used to explain the study and obtain informed consent. [17] Before finalising consent, the AHLO will be required use the “teach back” method and ask the caregiver to explain in their own words what the research study is asking them to do, including risks and processes involved [18].

It is anticipated that a high proportion of caregivers will consent to be a part of this trial; however, we anticipate a high drop-out rate due to the length of the trial, anticipated social issues and previously documented high drop-out rates in a similar study [14]. A high attrition rate (approximately 50%) has been factored into the sample size calculations below.

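### The primary Mann-Whitney test can rank only observed scores, which does not fit an ITT promise covering all children when about half are expected to be lost

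*Protocol article*

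**What the plan says.** All from the protocol article.

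- **Statistical analyses.** The "Mann Whitney U test will be used to determine if differences in quality of life measures exist between the ICCC versus self-directed care groups". No visit, covariate or hospital term is attached. The same paragraph declares all analyses ITT, with every subject compared as assigned, including those who withdraw or are lost.
- **Recruitment.** "A high attrition rate (approximately 50%) has been factored into the sample size calculations below".
- **Sample size and statistical power.** "We plan for a total sample size of 112 children", with "80% power to detect a mean effect difference of 15 between groups on the quality of life scale" "at 0.05 significance level". No SD is given.
- **Safety considerations/patient safety.** Self-directed children may move to the ICCC after 6 months; if they do, their 12-month data are left out of the final analyses.
- **Randomisation, ICCC pathway and Outcome measures.** Allocation is opened directly after consent. The first PedQOL score comes at 1 week. The visit descriptions then place PedQOL at 6 and 12 months.

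**The concern.** The named test and the ITT statement do not fit together at the expected loss. A Mann-Whitney test ranks scores that exist. Unless a further method supplies the missing ones, about half the randomised children drop out of the primary comparison. Randomising more children restores precision but does not protect against selective loss. If who stays depends on how the child was doing, and does so differently in the two arms, the comparison is biased.

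The rule on switchers adds a second problem that needs no inference: data that have been recorded are removed because of a choice made after randomisation, in one arm only.

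The test also sets aside information the trial collects. A child seen at 6 but not 12 months contributes nothing to a 12-month comparison, and hospital is ignored. Sizing is on a mean difference of 15, but the test as named returns no mean difference or interval.

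**Working it through.** **1. The plan's own figure.** Inputs: difference 15, alpha 0.05 (two-sided assumed), power 80%, 50% attrition, 1:1. The SD is not given and must be assumed.

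n per arm = 2 × (1.960 + 0.842)² × (SD/15)². With SD 20 this is 27.9, so 28 per arm, 56 in total, and 56/0.5 = 112. Back-solving from 28 per arm gives SD 20.03. Other SDs, inflated the same way, give:

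| SD | Randomised |
|---|---|
| 15 | 64 |
| 18 | 92 |
| 20 | 112 |
| 22 | 136 |
| 25 | 176 |

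SD 20 is therefore a plausible reading, not a verified one. (SD 23 with inflation by 1.5 instead of division by 0.5 gives 74 × 1.5 = 111, also close.) On the SD 20 reading, the stated power rests on 56 observed children.

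**2. Power of the named test (SD 20, 28 observed per arm, normal scores).** The two-sample t-test has 79% power. Mann-Whitney has 76% by simulation, or 78% using its asymptotic efficiency of 3/π = 0.955. Sizing with that efficiency gives 27.9/0.955 = 29.2, so 30 per arm and 120 randomised.

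**3. Bias from selective loss at 12 months.** Assumptions: SD 20; loss driven by a latent variable correlated 0.7 with the 6-month score, low scorers being lost; correlation r between 6- and 12-month scores of 0.5 to 0.7; no true effect.

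With a fraction p lost, the observed mean in an arm is too high by 20 × r × 0.7 × φ(z_p)/(1 − p).

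- p = 0.4: 0.7 × 0.386/0.6 = 0.451
- p = 0.6: 0.7 × 0.386/0.4 = 0.676
- Between-arm bias at 40% versus 60% loss: 20 × r × (0.676 − 0.451), which is 2.3 points at r = 0.5 and 3.2 at r = 0.7
- Equal loss by the same mechanism in both arms: the errors cancel and the bias is about 0. A separate null simulation, with about 50% loss depending on baseline alike in both arms, gave 4.8% rejection.

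Regressing on the observed 6-month score, as a likelihood model does implicitly, brings the error to about 0. That follows from the assumption that loss depends only on a score the model sees.

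**4. Where a model does not help.** Let loss depend on the unobserved outcome itself, with the same 0.7. One arm's mean at 50% loss is then off by 20 × 0.7 × 0.399/0.5 = 11.2 points. Adjusting for an earlier score correlated 0.5 to 0.7 still leaves about 7 to 9.

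**5. What a baseline score would add.** With a pre-allocation score correlated r with the outcome, the standardised effect becomes 0.75/√(1 − r²). At 28 per arm (t-test power):

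| r | Power |
|---|---|
| 0.3 | 82% |
| 0.5 | 89% |
| 0.6 | 93% |
| 0.7 | 97% |

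No such score is planned, so these figures are conditional on collecting one.

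**The case against.** The article does not say that the test is run on completers or at a single visit. It is a condensed document; imputation, sensitivity analyses and interval estimates are commonly left to a full protocol or SAP, and a rank test can be applied to imputed data or reported with a location-shift interval. Comparing children in their assigned arms is analysis by allocation, and a Mann-Whitney test by arm does not breach that. The test is valid for a bounded 0 to 100 score. No stratification by hospital is described that would oblige site adjustment. Nor is unequal loss shown: the text reminders and three call attempts are not described differently by arm, and medical students make the PedQOL calls.

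Much of this stands. A reader might infer that the plan commits to a completer analysis; it does not say so, and the absence of a missing-data method is not in itself the point. What remains is what the article does fix: an unadjusted rank test as the primary method, a promise covering children who are lost, and attrition met in the stated plan by a larger sample. Unequal loss is possible rather than established: only ICCC families have the liaison officer's help, and the article links expected drop-out partly to social issues. The switching rule is explicit and does not depend on any unseen document.

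**Conclusion.** The point holds as a mismatch between the named test and the stated ITT analysis, and as a choice of a weaker method where a better one is cheap. It is a recommended change, not a demonstrated bias.

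Under unequal loss (40% versus 60%), SD 20 and the stated correlations, the bias at 12 months is about 2 to 3 points, roughly a fifth of the 15-point target at most. With equal loss and no effect it is about 0. Power is about 76% against the stated 80%, also at SD 20; the shortfall is small and moves with the SD.

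Two stronger readings are not supported. A reader might take the error in one arm's mean at 50% loss (about 5.6 to 7.8 points in the working's model) as bias in the treatment effect; it would be that only if the other arm had no comparable loss. A reader might also expect power of 89% to 97% from changing the test alone; that needs a PedQOL score taken before allocation, and the first planned score follows open allocation. Finally, the bias illustration applies to 12 months. If 6 months is the named visit, the only earlier score is the one at 1 week, and a child with neither a 6- nor a 12-month score adds nothing to the proposed model.

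**What to change.** - Make the primary analysis a mixed model for repeated PedQOL scores at 6 and 12 months, with arm, visit, arm × visit and hospital, including every child with any follow-up score. Report the adjusted mean difference with a 95% interval at one named visit.
- Keep the Mann-Whitney test as a sensitivity analysis.
- Add a delta-adjusted multiple-imputation analysis that assumes worse scores for lost children, varied by arm, since the model does not cover loss driven by unobserved scores.
- Reconcile the exclusion of switchers' 12-month data with the ITT statement. The 6-month visit comes before the permitted switch, which bears on the choice of named visit.
- If PedQOL can be taken before the envelope is opened, add it as a covariate (interacting with visit). The 1-week score should not be used as that baseline.

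Cost: revised wording, a little more programming, and reliance on missing at random for the primary result. The optional baseline score adds one questionnaire at enrolment.

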## Methods

### Aims

This randomised controlled trial protocol investigates the cost-effectiveness of an integrated care pathway between hospital and primary care partnerships in improving health and social outcomes in children with chronic health conditions. More specifically, our objectives are to: (1) determine if the ICCC results in better health outcomes for children with chronic health conditions, compared to a self-directed care pathway; and (2) determine the cost-effectiveness of the ICCC using health economics data. We hypothesize that: (a) Children who access the ICCC will have improved quality of life and behavioural scores than children who access the self-directed care pathway; and (b) the ICCC pathway is more cost-effective than the self-directed care pathway.

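### The analysis stated for the cost-effectiveness objective builds a quality-of-life prediction index and cannot test whether ICCC is more cost-effective than self-directed care

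*Protocol article*

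**What the plan says.** In the Protocol article, Aims gives two objectives. The second is to "determine the cost-effectiveness of the ICCC using health economics data", and hypothesis (b) is that "the ICCC pathway is more cost-effective than the self-directed care pathway". Background also presents the trial as an evaluation of cost-effectiveness.

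Statistical analyses names a Mann-Whitney U test between arms on quality of life for the primary objective. For the secondary objective it gives a "univariable analysis to determine which health economic parameters (e.g. missed school days, number of hospital admissions) are related to higher quality of life scores". This is followed by stepwise regression and areas under the ROC curve, "to determine a clinical prediction index for higher quality of life scores". Candidates are the significant factors, those meeting the P < .25 "level in the univariable analysis and other variables known to have a strong association with poorer health outcomes". The success rule reads: "An aROC of ≥0.75 will be considered a clinically relevant cut-off score".

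Outcome measures lists the secondary outcomes as numbers of specialist appointments, GP visits and hospital admissions, together with "absent school days, caregiver missed employment days, school suspensions including duration in days and services currently accessed at the time".

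**The concern.** A claim that one pathway is more cost-effective than another needs a difference in cost and a difference in effect between the randomised groups. The analysis stated here asks something else: which resource-use counts go with better quality of life across the children studied. If it is carried out as written, the headline aim gets no answer from the analysis assigned to it.

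Two further weaknesses follow. First, none of the listed outcomes records AHLO time, although access to the AHLO's coordination is what distinguishes the arms (Self-directed care pathway). Second, the index would be called clinically relevant on an aROC threshold for which no correction is mentioned, after data-driven selection in a small sample. It also needs a binary outcome, while PedQOL runs from 0 to 100 and no cut-point for higher scores is given.

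**Working it through.** **1. Objective against analysis.**

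| Needed for hypothesis (b) | In the analysis stated for the secondary objective |
|---|---|
| Contrast between ICCC and self-directed care | None; arm does not appear |
| Cost per child | None; inputs are counts and days |
| Incremental cost and incremental effect | None; the output is a prediction index and an aROC |

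That the secondary objective means objective (2) is an inference. It is a strong one: Aims lists only two objectives, and the analysis is built on health economic parameters.

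**2. Resources captured.** Under the ICCC pathway, GP visits, admissions and specialist appointments come from Medicare forms. GP consults arranged for ICCC children should therefore enter the data. AHLO time has no counterpart among the outcomes. The pathway description says that the processes used by the AHLO and their outcomes are documented, but it does not mention hours.

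**3. Period covered.** The pathway description collects Medicare, school, employment and services data at 1 week, 3 months and 6 months. At 12 months it describes only PedQOL, SUDS and locus of control. Outcome measures nevertheless lists resource use at 12 months.

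**4. Number of children behind the index.** Sample size and statistical power gives 112 children, 80% power, a difference of 15, a 0.05 level and 50% attrition. No SD is stated. Assuming a two-sided test and 1:1 allocation, n per arm = 2 × (1.960 + 0.842)² × SD² / 15².
- SD 20: 2 × 7.849 × 400 / 225 = 27.9, so 28 per arm and 56 in all; 56 / (1 − 0.5) = 112, the stated total.
- SD 19 gives 26 per arm and a total of 104; SD 21 gives 31 per arm and a total of 124.

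The stated total thus fits an SD of about 20 and leaves about 56 completers.

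**5. Can noise reach 0.75?** Outcome measures lists 7 parameters, or 8 if number and duration of suspensions are counted separately. Simulation used 2,000 runs per setting, independent predictors unrelated to outcome, a univariable logistic screen at P < .25, then a multivariable logistic model with its aROC read from the same data. The median split, the elimination rule and the number of forced variables are assumptions, because the article states none of them. Share of trials with apparent aROC ≥ 0.75:

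| Setting | Screened factors kept | Backward elimination at P < .05 |
|---|---|---|
| 56 children, 7 candidates | 8% | 3% |
| 56 children, 8 candidates | 11% | 4% |
| 56 children, 7 candidates + 3 forced | 24% | 12% |
| 56 children, 7 candidates + 5 forced | 42% | 24% |
| 56 children, 7 candidates, 25% classed as higher | 19% | 7% |
| 112 children, 7 or 8 candidates | 0.2% or 0.3% | 0.0% |

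Forced variables stand for the literature-based ones that the article allows. Monte Carlo error is about 1 percentage point.

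**The case against.** The strongest reply is that an article condenses. Unit costs, incremental ratios and acceptability curves are usually left to a full protocol or SAP. The opening sentence of Statistical analyses says that all analyses compare children in their assigned groups, and the Abstract speaks of economic outcomes compared with self-directed care. The index also has a use of its own: the Discussion wants to learn which families can navigate care unaided and which need more support.

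Part of this stands. A comparison of resource use between arms is evidently intended, and costing detail missing from an article is no fault. But the article does not defer the analysis for this objective. It states one, and that one answers a different question. The general intention-to-treat sentence does not repair it, because the analysis then described compares no groups. An unseen SAP would have to replace or add to this text.

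On the index, the reply is largely right about size. With only the listed parameters and elimination at P < .05, noise passes in 3–4% of trials. Resource-use counts are plausibly correlated; at an assumed correlation of 0.3 the rate is about 2–3%. The figure of 56 is the anticipated attrition, and earlier visits may retain more children.

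**Conclusion.** The mismatch holds and needs no simulation: the analysis stated for the secondary objective cannot produce evidence for or against hypothesis (b). It rests on one inference, that this objective is objective (2). The powered comparison on quality of life is unaffected.

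Three stronger readings are tempting, but the documents do not support them.
- A reader might infer that the trial is bound to end without any economic estimate. An unseen plan could supply one; the finding concerns the analysis that this article states.
- A reader might infer that ICCC would appear to cost nothing. Arranged GP consults should be counted as GP visits. What is missing is AHLO time, and any part of the multidisciplinary meeting not recorded as a GP visit. The cost would be understated, by an amount the article does not let us calculate.
- A reader might infer that the 0.75 rule is routinely met by noise. Under the median split and 56 completers the range is about 3–11% for the 7–8 listed parameters. It rises to about 12–42% only if 3–5 further variables are forced in, and is under 1% with 112 children and 7–8 candidates. The article gives no basis for a much longer candidate list.

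The aROC issue is therefore supporting; the objective and its analysis are what must be changed.

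**What to change.** **Objective (2).** State as its analysis a between-arm, as-randomised comparison of cost per child and PedQOL.
- Cost per child is the listed resource use at fixed unit costs plus AHLO time. Add time to the process record that the AHLO already keeps.
- Report incremental cost and incremental PedQOL with bootstrap intervals.
- Set the horizon at 6 months, the period for which resource collection is described. If 12 months is wanted, the 12-month procedures and Outcome measures must first be reconciled. The analysis would also have to address the option, under Safety considerations, for self-directed families to switch after 6 months, with their 12-month data then left out.

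**Prediction index.** Label it exploratory, fix the quality-of-life cut-point in advance, and apply 0.75 only to an optimism-corrected aROC, with screening and selection repeated in each bootstrap resample.

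**Cost.** A small time-recording burden for the AHLO and modest analysis work. Apart from AHLO time, the resource data to 6 months are already planned. The corrected aROC will look less favourable than the apparent one.
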